**Fig 1 pone.0273290.g001:**
[figure not shown]
SPIRIT flow diagram: Schedule of enrollment, interventions and assessments. CFS, Computer Fluency Scale; EQ-5D-3L, EuroQol 5-Dimensions 3-Levels Questionnaire; GAD-2, Generalized Anxiety Disorder Questionnaire-2; PHQ-2, Patient Health Questionnaire-2; PSS-4, Perceived Stress Scale-4; GSES-12, General Self-Efficacy-12; HES, Health Empowerment Scale; SUS, System Usability Scale; TUQ, Telehealth Usability Questionnaire; MAUQ, mHealth App Usability Questionnaire; and CSQ, Client Satisfaction Questionnaire. *This instrument will be administered in the Adhera MejoraCare condition.

The intervention or follow-up will be discontinued if: a) the participant withdraws consent; b) the RCT is discontinued (e.g., due to poor patient recruitment, technological problems with the app that delivers the intervention); and c) the principal investigator or project administrator determines the need to discontinue the RCT (e.g., due to ethical and privacy issues, funding problems).

### Ethics and auditing

The study follows the guidelines of the Helsinki Declaration [31]. All the researchers will follow the guidelines for Good Clinical Practice [32], and the Ethical Principles and Code of Conduct for Psychologists of the American Psychological Association [33]. As noted, all the participants will be volunteers, and they will not receive any compensation for their participation. They will sign informed consent once the study and its conditions have been explained. Participants will be able to withdraw from the study at any time, without giving any reason and with no consequences. This study was approved by the Ethics Committee of Research in Humans of the Ethics Commission in Experimental Research of University of Valencia, (date: December 4, 2020; register number: 1472070) and the Ethics Committee of the Autonomous University of Encarnación. Besides, the study was registered in the United States National Institute of Health Registration System with Clinical Trials Registration Number: NCT04659746 (https://clinicaltrials.gov/ct2/show/NCT04659746). No audit has been planned at this time.

### Intervention

#### Experimental group

Adhera® MejoraCare Digital Program is an mHealth solution designed to raise awareness, educate and empower patients in the management of CD in the presence of the COVID-19, promoting behavioral changes in their lifestyle and emotional coping. A holistic "empowerment" approach based on cognitive-behavioral techniques (CBT) will be adopted to activate and empower CD management in patients. It will include evidence-based CBT techniques aimed at intervening on 1) cognitive, 2) emotional, and 3) behavioral variables, in three areas: COVID-19 psychoeducation, well-being, and lifestyle, following the guidelines from the World Health Organization for COVID-19 [34], Ryff’s well-being model [35] and health behaviour models for behaviour change [36]. Table 1 shows the contents included in the Adhera® MejoraCare Digital Program.

**Table 1 pone.0273290.t001:** Contents of the Adhera® MejoraCare Digital Program.

Module Topic	Subtopics
**COVID-19**	• What is the new coronavirus and COVID-19
	• Prevention measures for COVID-19
	• Day-to-day prevention
	• People at risk for COVID-19
	• If you have symptoms: quarantine
	• Care of the quarantined patient
	• Children and adolescents in confinement
**Well-being**	• Emotional management during confinement
	• Coping with grief
**Lifestyle**	• Healthy nutrition under challenging times
	• Physical activity at home

Adhera® MejoraCare Digital Program includes the following functionalities (Fig 2): a) COVID-19 symptom monitoring; b) patient empowerment components (including educational methods and instructions to promote behavioral changes to establish and maintain a healthy lifestyle that minimizes the risk of contagion/propagation of the disease and improves patients’ quality of life); c) self-assessment tests to check and reinforce acquired knowledge; and d) tailored motivational messages that help to acquire lifestyle habits to prevent the spread of the COVID-19.

**Fig 2 pone.0273290.g002:**
[figure not shown]
Functionalities of the Adhera MejoraCare solution. Left: Symptom’s monitoring. Center: Patient empowerment categories in the educational section. Right: Educational units included in the ‘‘How to protect from coronavirus” category.

An AI-driven algorithm will be used for selecting and delivering tailored messages based on the user’s profile and scientific evidence, following the integrated behavior change model "I-Change". This algorithm is based on the work of Hors-Fraile et al. [37], and it has been successfully clinically validated for promoting smoking cessation in a randomized clinical trial [38].

The mobile app included in this mHealth solution will be downloaded and installed like any other commercial app from Google Play. The participant will receive an email from the research team with instructions on how to install the application. Specifically, the download link and an individual access code will be provided. The code can only be used once, which ensure that only one device can be use which the specific code. In case that the participant changed the mobile device during the study they can request an additional code, and this change will be track down to prevent data lose.

#### Control group

The WL group will not receive any intervention during the 1-year study period.

### Measures

#### Screening related measures

*Sociodemographic variables and medical history*. Personal data will be collected, including information such as age, gender, profession, marital status, employment status, level of studies, diagnosis of CD and its duration, clinical course, medication, diagnosis of mental disorder, and pregnancy.

*User’s technological profile*. The Computer Fluency Scale (CFS; [39]) is a self-report scale that assesses computer comfort and self-report of computing ability through 7 items rated on a 5-point Likert scale ranging from 1 (strongly disagree) to 5 (strongly agree). A high score indicates greater comfort with computers.

*Ad hoc* questionnaire designed to evaluate the frequency and the perceived ability to use a mobile phone. It is composed of 9 items (e.g., To what extent do you feel capable of using technologies? Have you ever used a computer?).

#### Primary outcome measure

*Quality of life*. The EuroQol 5-Dimensions 3-Levels Questionnaire (EQ-5D-3L; [40, 41]) is a self-report questionnaire that measures health-related quality of life and enables conversion to utility scores to calculate Quality-Adjusted Life-Years (QALYs) [42, 43]. It measures five dimensions of health: mobility, self-care, usual activities, pain/discomfort, and anxiety/depression. Each category consists of 1 item, ranging from 1 (no problems) to 3 (lots of problems). The second part of the EQ-5D-3L is a 20-centimetre vertical Visual Analogue Scale (VAS), ranging from 0 (worst imaginable health) to 100 (best imaginable health). The individual must mark the point on the scale that best reflects the assessment of their global health status today. The VAS’s use provides a complementary score to the descriptive system of the self-assessment of the individual’s health status [44].

#### Secondary outcome measures

*Anxiety symptoms*. The Generalized Anxiety Disorder Questionnaire-2 (GAD-2; [45, 46]) is a self-report measure that contains 2 items that assess anxiety symptoms. The items are scored on a 4-point Likert scale, ranging from 0 (no days) to 3 (almost every day), where a high score indicates greater anxiety symptoms.

*Depressive symptoms*. The Patient Health Questionnaire-2 (PHQ-2; [47, 48]) is a self-report measure that consists of 2 items that assess depressive symptoms. The items are scored on a 4-point Likert scale, ranging from 0 (never) to 3 (almost every day), where a high score indicates greater levels of depressive symptoms.

*Stress*. The Perceived Stress Scale-4 (PSS-4; [49, 50]) is a self-report scale that consists of 4 items that measures the degree to which life situations are considered stressful. The items are scored on a 4-point Likert scale, ranging from 0 (never) to 4 (very often), where a high score indicates a high perception of stress.

*Self-efficacy*. The General Self-Efficacy Scale-12 (GSES-12; [51, 52]) is a self-report questionnaire consisting of 12 items grouped into three factors: initiative (willingness to initiate behaviour), effort (willingness to make an effort to complete the behaviour) and persistence (persevering to complete the task in the face of adversity). The items are scored on a 5-point Likert scale, ranging from 1 (it never happens to me) to 5 (it always happens to me), where a high score indicates higher levels of self-efficacy.

*Health empowerment*. The Health Empowerment Scale (HES; [53]) is a self-report measure that assesses health-related empowerment (e.g., health-related satisfaction, goal achievement, stress management, social support, self-motivation, decision making). It consists of 8 items scored on a 5-point Likert scale ranging from 1 (strongly disagree) to 5 (strongly agree), where high scores are indicators of a higher level of health-related empowerment.

#### mHealth solution usability and treatment satisfaction

*System usability*. The System Usability Scale (SUS; [54, 55]) is a self-reported measure that assesses the intervention’s overall usability. It is a 10-item scale, measured on a 5-point Likert scale ranging from 1 (strongly disagree) to 5 (strongly agree). Total SUS scores range from 0 to 100. The questionnaire is designed to be answered after the user’s interaction with the system.

*Telehealth usability*. An adaptation of the original Telehealth Usability Questionnaire (TUQ; [56, 57]) will be used in this study. This self-report questionnaire provides information on the telehealth system’s usability (usefulness, ease of use, effectiveness, reliability and satisfaction). It consists of 16 items on a 7-point Likert scale that range from 1 (strongly disagree) to 7 (strongly agree). The total score ranges from 7 to 112. Higher scores are indicators of higher usability of the telehealth system.

*mHealth solution usability*. The mHealth App Usability Questionnaire (MAUQ; [58]) is a self-reported instrument that assesses the usability of mHealth solutions. It consists of 26 items with 3 subscales (ease of use, interface and satisfaction, usefulness) on a 7-point Likert scale ranging from 1 (strongly disagree) to 7 (strongly agree). The total score ranges from 21 to 147. High scores are indicators of higher usability of mHealth solutions.

*Client satisfaction*. The Client Satisfaction Questionnaire (CSQ; [59–61]) is a self-reported questionnaire that assesses the general satisfaction of the patient with health and human services. It consists of 8 items on a 4-point Likert scale ranging from 1 (lowest score per item) to 4 (highest score per item). The total score ranges from 8 to 32, with higher values indicating higher satisfaction.

#### Adhera® MejoraCare Digital Program adherence

The number of times the participant uses the mHealth solution will be recorded and tracked.

### Data management

Online data collected from LimeSurvey will be stored at protected servers of the University of Valencia. Only individuals authorized by the principal investigator will have access to the database. After completing the assessment points, authorized individuals will download the database in a SPSS format that will be automatically saved onto a password-protected cloud server of the University of Valencia (nÚVol, https://nuvol.uv.es). Pseudonymization will be used for the processing of participants’ personal data while the study is active. Once the study has finished, an anonymized copy of the database will be stored at the University of Valencia for up to 5 years after the project ends, following the principles of the European GDPR 2016/679.

### Analysis

First, descriptive statistics and normality assumptions will be examined. In case assumptions are met, t-tests for independent samples, ANOVAs, and chi-square analysis will be calculated to observe differences between groups at baseline in quantitative and categorical variables. In case normality assumptions are not met, robust t-test for independent samples and robust ANOVAs will be calculated [62]. Effect size will be quantified using Cohen’s d (d; [63]) or its robust equivalent (*d*_*R*_; [64]) when normality assumptions are not met, and robust estimations are employed. Independent-sample t-tests and chi-squared tests will be also performed to check that there are no significant differences in sociodemographic characteristics of the participants between groups that can act as confounding variables (i.e., age, gender, year and CD diagnosis).

Then, the multivariate normality assumption on the primary and secondary outcome measures will be tested before computing the linear mixed models. If the assumption is met, linear mixed models will be performed for each dependent variable, considering temporal moments as an intra-group factor and condition as an inter-group factor, using the False Discovery Rate (FDR) adjustments for post-hoc multiple comparisons. Otherwise, their mixed robust equivalents will be calculated [62].

In addition, multiple hierarchical regression models will be used to identify possible predictors of evolution in the primary and secondary measures. In particular, it is expected that characteristics as the gender, age, the CD, and user’s technological profile will act as predictor for the level of adherence to Adhera® MejoraCare Digital Program intervention, and the change in quality of life, self-efficacy, health empowerment, and anxiety and depression symptomatology. Finally, moderation analyses will be performed to test whether the gender, age, the CD, user’s technological profile and level of adherence moderate the intervention’s effect on quality of life, self-efficacy, health empowerment, and anxiety and depression symptomatology. These analyses will be performed using the macro PROCESS (version 4.0, https://processmacro.org/). The conditional effects of condition on the dependent variables at medium (the mean), low (−1 SD), and high (+1 SD) levels of the moderator variables will be examined with the “pick-a-point approach”.

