### Sample size

Sample size calculation was done using G*Power [24], based on the primary endpoint. Specifically, sample size was calculated for a mixed ANOVA design, with the between effects being the experimental condition (2 groups) and the within-effects being the different time points. As we were interested in the interaction between experimental group and time effect, 8 measurements were specified (2 groups x 4 time points). With a power of 80%, and an alpha level = .05, and an expected moderated effect size of d = .50 according to similar studies [25], the required sample size is 74 participants (37 per condition). Taking into account a potential dropout of 20% according to literature [26, 27], this study will recruit a total of 94 participants (47 per condition).

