The general practitioners and specialists participating in the study will identify patients belonging to the high-risk group for CDs. Once identified, the physicians will make a face-to-face appointment with the potential candidates to explain the conditions of participation in the research study. Those interested in participating will sign the informed consent form and complete a brief questionnaire to verify compliance with the inclusion criteria: men and women; 18 years and older; CD diagnosis (i.e., cardiovascular disease, chronic obstructive pulmonary disease, diabetes, hypertension, and cancer); no severe psychiatric comorbidities (i.e., substance dependence, bipolar affective disorder, obsessive compulsive disorder, psychotic illness); and own an Android smartphone. Physicians participating in the study will have access to the patient’s medical history to check for the presence of a diagnosis of mental illness and the presence of severe psychiatric comorbidity. Subsequently, those who meet the criteria for participation in the study will complete the measures corresponding to the baseline through the *LimeSurvey* platform via a link that will be sent to the participant’s email address. Afterwards, participants will be randomized to one of the two conditions (intervention or control). An independent researcher from Valencia University will generate a permuted block randomization with fixed and concealed block length (20 participants per block), and with an allocation ratio of 1:1, using a computerized random number generator (Random Allocation Software 2.0 [30]). For methodological reasons, participants will not be blind to the condition. All patients will be assessed at 1-, 3-, 6- and 12-months from the time of randomization via the *LimeSurvey* platform. Fig 1 shows SPIRIT flow diagram of the study.

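### Baseline significance tests are planned to rule out confounding after randomisation, and the efficacy model as described does not adjust for the baseline score, so it gives up part of the available precision

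*Protocol article*

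**What the plan says.** The Analysis section of the protocol article begins with t-tests, ANOVAs and chi-square tests between the arms at baseline. It then adds tests of age, gender, year and chronic disease diagnosis, to "check that there are no significant differences in sociodemographic characteristics of the participants between groups that can act as confounding variables". It does not say what follows from a significant or a non-significant result.

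The efficacy analysis is a linear mixed model for each outcome, "considering temporal moments as an intra-group factor and condition as an inter-group factor", with a robust mixed equivalent if multivariate normality fails. No baseline covariate is named. Age, gender and diagnosis reappear only in the later predictor and moderation analyses.

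Four other places bear on the point:

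- The section on population and recruitment has participants complete the baseline measures first: "Afterwards, participants will be randomized to one of the two conditions (intervention or control").
- The Abstract defines the primary outcome as a change in EQ-5D-3L, and Research design lists baseline among five repeated measures.
- Sample size names the effect of interest ("As we were interested in the interaction between experimental group and time effect") but counts four times: "8 measurements were specified (2 groups x 4 time points").
- The first hypothesis in the Introduction places the main comparison at 1 month.

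**The concern.** There are two linked weaknesses.

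**The tests.** When arms are formed by randomisation after baseline, the null hypothesis of a baseline test is true by design. A significant result is a chance event. A non-significant result mostly reflects the sample size. Neither says whether a prognostic variable is unbalanced enough to matter for the outcome, so the stated purpose cannot be met. The text also leaves open what a significant result would lead to.

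**The model.** The baseline EQ-5D-3L score is collected before randomisation and is likely to be among the best predictors of the later score. With only time and condition as terms, it is used by subtraction or not at all. Either way the 1-month estimate has a wider confidence interval than the same data allow, in a trial planned on 37 analysed participants per arm.

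**Working it through.** **Inputs.** From Sample size: α = 0.05 (taken as two-sided), power 80%, d = 0.50, 37 per arm analysed, 47 per arm recruited. Assumed, because the document gives neither: the correlation ρ between the baseline and 1-month scores (range 0.3 to 0.7), and d measured in raw-score SD units. Equal variances at the two times are also assumed.

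**1. The plan's own figure.** With f = d/2 = 0.25, two groups, m = 8 measurements and ρ = 0.5, the between-group repeated-measures test has λ = f²·N·m / (1 + (m − 1)ρ) = 0.0625 × 74 × 8 / 4.5 = 8.22, and power 0.808. N = 72 gives 0.797, so N = 74 is reproduced. Dropout: 37 / 0.8 = 46.25, rounded up to 47 per arm, 94 in total. (The group-by-time interaction that the text names would give 24 with two groups and four times. That mismatch is a separate matter; here 37 per arm serves only as the analysed size.)

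**2. What the time-by-condition model estimates.** In 100 simulated trials (37 per arm, five times including baseline, random intercept, complete data, ρ = 0.5), the interaction estimate at 1 month equalled the difference in mean change from baseline. The largest gap was 6 × 10⁻¹⁵. The mean standard error was 0.231, against 0.201 with baseline as a covariate. Theory agrees: √(2 × 1.00/37) = 0.232 and √(2 × 0.75/37) = 0.201.

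**3. Variance of the 1-month effect**, relative to an unadjusted comparison of follow-up scores:

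- unadjusted: 1
- change score: 2(1 − ρ)
- baseline as covariate: 1 − ρ²

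The share of attainable precision lost by the change score is 1 − (1 − ρ²)/[2(1 − ρ)] = (1 − ρ)/2. The share lost by the unadjusted comparison is ρ².

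**4. Power**, from the noncentral t distribution with 72 degrees of freedom and noncentrality d·√(n/2)/√v. For v = 1 this is 0.50 × √18.5 = 2.15. For v = 0.75 it is 2.15/√0.75 = 2.48. The one degree of freedom spent on the covariate is ignored.

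| ρ | v, change | v, adjusted | Precision lost by change score | Power, change | Power, adjusted | Power, unadjusted |
|---|---|---|---|---|---|---|
| 0.3 | 1.40 | 0.91 | 35% | 43% | 60% | 56% |
| 0.5 | 1.00 | 0.75 | 25% | 56% | 69% | 56% |
| 0.7 | 0.60 | 0.51 | 15% | 78% | 84% | 56% |

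At ρ = 0.5 the change score gains nothing over ignoring baseline, and below 0.5 it does worse. At that value adjustment is worth 1/0.75 = 1.33 times the sample.

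**5. The scale of d.** If d = 0.50 is instead in SD units of the change score, change-score power is 56% at every ρ. Adjusted power has noncentrality 2.15 × √[2/(1 + ρ)] and is 75%, 69% and 63% at ρ = 0.3, 0.5 and 0.7. The share of precision lost does not change.

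**6. What the baseline tests can detect.** With 47 per arm an observed difference reaches significance only beyond 1.986 × √(2/47) = 0.41 SD (with 37 per arm, 0.46 SD). A true difference of 0.3 SD would be flagged with probability 30% (25% with 37). In the other direction, if the four listed variables were tested independently at 0.05, correct randomisation would give at least one significant result with probability 1 − 0.95⁴ = 18.5%.

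**The case against.** The strongest reply is that the article condenses a fuller plan. How baseline enters a mixed model, and which covariates it carries, are often left to the SAP. The Analysis section does not list the time levels, and its model sentence does not mention an interaction. The four time points under Sample size could be the four follow-ups, leaving baseline free to be a covariate. This stands as far as certainty goes: baseline as a time level is an inference from the Abstract and Research design. It does not remove the point. On one reading the effect is a change score, and on the other it is unadjusted as the model is written. The baseline tests are stated outright, with their purpose.

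Stronger readings are tempting, and the document does not support them:

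- *The model discards the baseline information.* A time-by-condition contrast uses it by subtraction and loses a share (1 − ρ)/2, which shrinks as ρ rises.
- *The tests stand in for adjustment, or adjustment will depend on them.* The text attaches no consequence to the tests.
- *The treatment comparison is biased.* Randomisation protects it on average under either reading.
- *Age, gender and diagnosis must be in the model.* No stratification by them is described and no gain from them has been quantified. Diagnosis has five listed categories, which would cost parameters in a trial of this size.

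It is also fair to say that the power figures concern one 1-month contrast, whereas the trial was sized on an effect over several times.

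**Conclusion.** The point holds in a limited form. The baseline tests are stated and cannot do what they are meant to do. The model as described leaves part of the precision of an already collected baseline score unused: 35%, 25% or 15% at ρ = 0.3, 0.5 or 0.7 for a change-score contrast, or ρ² (9%, 25%, 49%) if baseline is left out. In power at 1 month that is a gap of 17, 12 or 6 percentage points (unrounded) between change score and adjusted analysis, with d in raw SD units. The power figures depend on ρ and on the scale of d, neither of which the document gives, and the share lost depends on ρ alone. For any ρ between 0 and 1 adjustment is more precise than either alternative. Validity is not in question. It is an improvement that should be made before the data are analysed.

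**What to change.** 1. Delete the between-arm significance tests at baseline, and describe the arms with summary statistics.
2. State the time levels of the outcome model, and how baseline enters it. Either use the baseline score as a covariate with the four follow-ups as outcomes, or keep baseline as an outcome and constrain the arms to a common baseline mean.
3. Carry baseline adjustment into the robust alternative, naming a procedure that allows it.
4. Adjustment for further covariates is optional. Any that are used should be fixed in advance, and not chosen from baseline tests.

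The cost is wording in the analysis plan and, for item 3, the choice of a suitable robust method. No new data are needed, because the baseline scores are collected before randomisation.

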We would like to mention some possible limitations. First, the possible presence of a high dropout or attrition rate by participants from the mHealth solution intervention condition [67]. Second, the results of this RCT should be interpreted with caution as they are limited to only a few specific groups of CDs. Future research with mHealth solutions should focus on increasing the sample size and performing in-depth analyses on a wide range of CDs to draw more robust and generalized conclusions. Third, implementing mHealth technologies in a LMIC will represent a major challenge for both researchers and users given the characteristics of the context (e.g., Internet connectivity issues, experience with technology). Finally, it is worth mentioning that this study only includes participants with an Android smartphone, thus limiting the recruitment of potential users with smartphones with different operating systems such as iOS.

In conclusion, this study’s results could help understand better how to offer self-care strategies to people with CD and shed evidence on the impact of mHealth solutions on the management of chronic medical conditions in a LMIC during the COVID-19 pandemic.

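### The model for the primary outcome hangs on a normality test of the outcome scores, which tests the wrong quantity and leaves the primary analysis dependent on the data

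*Protocol article*

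**What the plan says.** The Analysis section of the protocol article sets a two-step rule. First, "the multivariate normality assumption on the primary and secondary outcome measures will be tested before computing the linear mixed models". Then: "If the assumption is met, linear mixed models will be performed for each dependent variable", with time as the within-participant factor and condition as the between-group factor. If the test fails: "Otherwise, their mixed robust equivalents will be calculated", citing the same reference as the robust t-tests and ANOVAs used for baseline comparisons. The paragraph before it makes the effect size follow the same switch: Cohen's d when normality holds, a robust d when it does not.

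The section does not name the test or its level. It does not say whether one joint test covers all outcomes or each is tested alone, nor whether arms are pooled.

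The outcomes differ widely in coarseness. For the EQ-5D-3L descriptive system the article states: "Each category consists of 1 item, ranging from 1 (no problems) to 3 (lots of problems". The same primary measure also includes a 0 to 100 VAS, and the article does not say which of the two scores is primary. The GAD-2 "is a self-report measure that contains 2 items that assess anxiety symptoms" and the PHQ-2 "is a self-report measure that consists of 2 items that assess depressive symptoms", each item scored 0 to 3. The remaining scales are longer: PSS-4 (4 items), HES (8 items) and GSES-12 (12 items).

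**The concern.** There are two faults. The first is the target of the test. A linear mixed model assumes normal residuals and random effects once arm and time are accounted for. It does not require the raw outcome scores to be multivariate normal. Because the plan fits a separate model to each dependent variable, it never relies on joint normality across different outcomes.

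The second is what the test decides. It selects the model for the primary outcome, and apparently the effect measure too. A reader of the protocol cannot say in advance whether the primary result will be a mixed-model contrast with d or a robust contrast with robust d. With test, level and scope unstated, two analysts could follow the text faithfully and reach different primary analyses. If a single joint test is meant, a two-item secondary scale could decide how quality of life is analysed.

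**Working it through.** **The plan's own figures.** The article gives no failure rate for the gate, so there is none to reproduce. The sample sizes used below come from the Sample size section: 74 required and 94 recruited. The second follows from the first: 37 / (1 − 0.20) = 46.25, rounded up to 47 per arm, and 2 × 47 = 94.

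**Score ranges from the stated items.**
- GAD-2 and PHQ-2: 2 items × 0–3 gives 0–6, seven possible values.
- EQ-5D-3L descriptive system: 5 items × 3 levels. Simulated as an item sum, because the article gives no value set.
- HES: 8 items × 1–5 gives 8–40. GSES-12: 12 items × 1–5 gives 12–60. VAS: 0–100.

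**Assumptions.** The article gives no score distributions, so three were tried.
- Symmetric items: about 10% at the GAD-2 floor, 2.5% with no EQ-5D problems.
- Mild skew: about 26% and 17%.
- Clear skew: about 40% and 33%.

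The tests were Mardia (skewness or kurtosis) and Henze-Zirkler, each at 5%. With 600 replicates, the Monte Carlo standard error is at most √(0.25/600) = 0.020, or 2 percentage points.

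**Each outcome tested over its five time points, n = 74** (percentage of runs failing, Mardia / Henze-Zirkler):

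| Score | Symmetric | Mild skew | Clear skew |
|---|---|---|---|
| GAD-2 type (PHQ-2 has the same structure) | 49 / 59 | 60 / 100 | 100 / 100 |
| EQ-5D item sum | 27 / 15 | 81 / 98 | 100 / 100 |
| PSS-4 | 16 / 7 | 22 / 14 | not reported |
| GSES-12 | 15 / 8 | 32 / 56 | not reported |

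For a VAS with mean 60 to 80 and SD 18 to 20, Mardia failed in 12% to 40% of runs.

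**One joint test of six outcomes at one time point, n = 74 to 94:**
- symmetric: Mardia 42–53%, Henze-Zirkler 15–19%;
- mild skew: 37–55% and 57–76%;
- clear skew: 97–100% by both.

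**Baseline for the test itself.** In this setting Mardia rejected about 11% of truly normal six-variable data. Taking all six outcomes at all five time points gives 30 variables; at n = 74 Mardia then rejected 89% of truly normal data. At that size its verdict says nothing about the data.

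**Reading.** Depending on test, scope, outcome and distribution, failure runs from about 7% to 100%. The choice of unnamed test alone moves the joint mild-skew result from 37–55% to 57–76%.

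**The case against.** The best defence is that both branches are named in advance, so this is a rule and not an absent analysis. It can also be said that, with only arm and time in the model, testing one outcome's repeated measures within each arm comes close to testing the model's assumption. Both points have force. But the text does not restrict the test to within arm or to one outcome at a time. Even a well-aimed check is a poor way to choose the primary method: it should prompt a sensitivity analysis.

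Several stronger readings are tempting and are not supported.
- **That the gate will almost surely fail and the mixed model will rarely be run.** Univariate Shapiro-Wilk rejected a single GAD-2 or PHQ-2 score in every run, even with symmetric items, but the plan calls for a multivariate test. Under symmetric items the EQ-5D item sum failed in only 15% to 27% of runs, and the VAS, if primary, is less prone still.
- **That the fallback is a trimmed-mean analysis of completers.** The article states neither trimming nor a complete-case restriction, and the cited reference is not at hand. Any loss from trimming would also depend on who benefits. With benefit confined to the lowest 30%, a 20% trimmed contrast was 0.028 against a mean difference of 0.044; with uniform benefit in another simulation it was 0.045 against 0.037.
- **That complete cases would fall below 74.** The stated 20% dropout leaves 0.80 × 94 = 75.2. Reaching about 64 needs an added assumption of 5% intermittent missingness at three visits (0.80 × 0.95³ × 94 = 64.5).
- **That the protocol expects dropout concentrated in the app arm.** The limitations paragraph mentions only "the possible presence of a high dropout or attrition rate by participants from the mHealth solution intervention condition", without comparing it with the waiting list.
- **That the choice waits on unblinded data.** The article does not say the check uses arm labels; a test on pooled outcomes would not need them.

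**Conclusion.** The point holds in a limited form. The Analysis section tests outcome scores where the model's assumption concerns residuals and random effects. It lets that test, with no name, level or scope, choose the primary model. The effect measure appears to switch with it, if the d or robust-d rule, stated alongside the baseline comparisons, is meant for the outcome analyses too.

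Failure is likely (about 60% to 100%) for the EQ-5D-3L item sum, GAD-2 and PHQ-2 if they show mild to clear skew. It is far less certain for PSS-4, GSES-12 and the VAS (roughly 7% to 56%) and for symmetric coarse scores (15% to 59%). These figures rest on assumed distributions, two chosen tests at 5%, and an item sum standing in for the EQ-5D index. The defect does not depend on a high failure rate: the less predictable the test, the less anyone can say beforehand which analysis is primary. It should be corrected, but it does not by itself show that the trial's result would be biased.

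**What to change.** In the Analysis section, delete the normality test as a condition for the model. State that the primary analysis, and the analysis of each secondary outcome, is the linear mixed model on all randomised patients using all available visits. Take inference from robust standard errors with a small-sample correction, or from the bootstrap. Name one effect measure in advance. Check the residuals of the fitted model instead of raw scores, and report the robust equivalent as a sensitivity analysis whatever that check shows.

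The cost is a few sentences and slightly more programming. Sample size, visits and data collection are unaffected.
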